#### 2.5.2. Exclusion Criteria

Patient with stomatitis or ulcerative gingivitis.Developmental abnormalities of enamel and dentin.Serious non-communicable medical conditions include cardiac failure and poor glycaemic control.Cavitated teeth missing greater than a third of the coronal tooth structure or having pulpal involvement. Pulp-exposed tooth, obvious discoloration, premature hypermobility, or presence of a periapical abscess or a sinus will be regarded as a tooth with pulpal involvement.Known silver allergy.During the intervention, if there is inadvertent pulp exposure, the patient will be excluded from the study.

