### 2.7. Interventions

After patient selection, the treatment will be given to the patient according to the selection process. The study participants will be allocated to either one of two parallel arms.

Study arm 1: will receive SDF application and ART restoration.

Study arm 2: will receive ART restoration.

All treatment will be done in a dental chair.

At the baseline visit, an assessment of cavitated caries lesions will be done on all the study participants. The ADA Caries Risk Assessment Form (Age > 6) would be used to assess the risk. Depending on the study arm, ART with or without SDF will be applied to selected teeth (Figure 1). The demographic features of participants and their caries status will be recorded.

*Procedure to be followed for study arm 1:*

A preoperative photograph of the selected tooth will be taken. The caries lesion entrance will be widened and with help of a dental hatchet, the thin unsupported frangible enamel will be removed. In the next step, the decayed tissue will be excavated with a spoon excavator, first at the dentin enamel junction and thereafter from cavity walls and the pulpal floor. The cavity will then be rinsed with water and air-dried, followed by isolation with cotton rolls.

*Application of Silver Diamine Fluoride*

Using a disposable micro applicator tip, the SDF (e-SDF, 38% silver diamine fluoride, Kids-e-dental LLP, Globus Medisys, Mumbai, India) will be applied to the walls of the prepared cavity for 10 s and allowed to air dry for one minute. One drop of 38% SDF solution (2.24 F-ion mg/dose) would be required per tooth. A saturated solution of potassium iodide (Lugol’s Iodine solution 5%, Bio balance, Pali Marwar, Rajasthan, India) will be applied with a different microsponge to decrease color change and will be repeated 1-3 times until no further black discoloration is observed [17].

*Placement of ART restoration*

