Glass ionomer cement (Glass Ionomer High Strength Posterior restorative, GC Corporation, Tokyo, Japan) will be prepared according to the manufacturer’s instructions. The restorative material will be placed into the prepared cavity using a plastic filling instrument. The press finger technique will be used for approximately one minute and the restoration will be coated with petroleum jelly. A carver would be used to remove the excess material. The height of restoration will be adjusted after the bite is checked using articulation paper. A photograph and a digital radiograph of the restored tooth will be taken after the procedure and at the end of the study.

*Procedure to be followed for study arm 2:*

*Placement of ART restoration*

A preoperative photograph of the selected tooth will be taken. The preparation of the cavity will be done as stated above using hand instruments. Conditioning of the prepared tooth surface will be done with an applicator tip saturated with the polyacrylic acid liquid for 10–15 s. Glass ionomer cement (GIC Fuji IX, G C CORPORATION, [name]) will be prepared according to the manufacturer’s instructions and placed into the cavity using a plastic filling instrument. The press finger technique will be followed, and the surface of the restoration will be coated with petroleum jelly. The bite will be checked using articulation paper and the occlusal adjustments will be done. A photograph and a digital radiograph of the restored tooth will be taken after the procedure and at the end of the study.

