### 2.12. Study Implementation

The adult patients visiting for routine dental care to dental school will be recruited for the study. A clinical examination will be carried out on prospective participants. If the individual satisfies the inclusion criteria, the participant will be informed of the options for caries prevention by ART ± SDF. If they agree, they would be offered the choice of participation in the trial and the consenting process will be followed. The patient screening will continue till the target population is attained (n = 220).

Enrolment of the study population will be done over 24 months and follow-up visits are expected to be completed at the end of the 30th month, which will be followed by analysis and report writing. The total study duration is of three years.

The selected participants for the trial will be randomly allocated to a study arm, as per computer-generated randomization. The randomization code will not be revealed to the principal investigator until the participant has been recruited into the clinical trial after all the baseline assessments are complete. This is to ensure allocation concealment. Opaque-sealed envelopes containing randomization codes, in compliance with the randomization list, will be employed for allocation concealment. The randomization will be conducted by the research assistant. The randomization list will remain with the trial coordinator for the whole duration of the research. Due to the apparent nature of the treatment involved, neither the study participant nor the principal investigator (PI) can be blinded.

The PI will be trained for the study requirements, standardized in the assessment of the coronal carious lesion, caries cessation, 38% SDF application and ART, or ART alone, eliciting the required details from the study subjects in a consistent replicable method, and counseling for compliance. The procedure to be conducted and the data to be collected at each study visit will be inspected in detail. During the training sessions, details about procuring and entering the quality data in the clinical record forms will also be discussed. Calibration of PI (AV) will be done before and during the study by another clinical expert (CJ) and reliability will be expressed using Cohen’s kappa statistic.

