## 4. Statistical Methods

The observed data will be coded, tabulated, and analyzed using Statistical Package for Social Sciences (version 20). We will assess the outcomes at two levels (the Tooth level and the Individual level). The Chi-square test will be executed to assess the bivariate association between the outcome and sociodemographic variables. Kaplan–Meier survival analysis will be conducted on the censored data for the survival of the restoration. The difference between survival curves will be assessed by the Mandel—Haenszel log-rank test. Factors affecting survival rates will be assessed using the Cox-proportionality regression method. Between the two groups, the arrest of active carious lesion and survival of the restoration will be compared on the 7th day, 30thday, and at the end of the 6th month of the study visit. If there is a variation in outcome in patients with multiple restorations, tooth level analysis will be carried out.

Subgroup analysis will be performed at the tooth level (type of cavity; class1 and class 2, maxillary and mandibular teeth, premolar and molar)

We intend to have two sets of analyses.

The intention-to-treat analysis (including all randomized patients irrespective of whether they have or have not received the prescribed treatment).The per-protocol analysis.

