## Figures and Tables

**Figure 1 mps-05-00087-f001:**
[figure not shown]
Study flow diagram.

**Table 1 mps-05-00087-t001:** Participant timeline.

	Enrolment	Allocation	Post Allocation			Close Out
Time Point	t-1	t0	t1 (7 days)	t2 (30 days)	t3 (6 months)	tx
*Enrolment*						
Eligibility screen	X					
Informed consent	X					
Allocation		X				
Caries excavation		X				
*Interventions*						
38% SDF + ART						
ART						
*Assessments*						
Baseline variables cavitated carious lesion	X		X	X	X	
Caries arrest			X	X	X	X
Survival of restoration			X	X	X	X

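### Exclusion for pulp exposure appears to fall after randomisation, which conflicts with the intention-to-treat definition and leaves excavation open to knowledge of the arm

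*Protocol article*

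**What the plan says.** The exclusion criteria (2.5.2) end with a rule that operates during treatment: "During the intervention, if there is inadvertent pulp exposure, the patient will be excluded from the study".

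Four places bear on when this happens relative to randomisation:

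- **2.7 Interventions, arm 1.** Excavation is part of the procedure for this arm and precedes the use of silver diamine fluoride (SDF): "the decayed tissue will be excavated with a spoon excavator, first at the dentin enamel junction and thereafter from cavity walls and the pulpal floor".
- **2.7 Interventions, arm 2.** The same preparation is part of this arm's procedure: "The preparation of the cavity will be done as stated above using hand instruments". Conditioning follows.
- **2.12 Study Implementation.** The code is withheld "until the participant has been recruited into the clinical trial after all the baseline assessments are complete". Excavation is not named as a baseline assessment. The same section says that "neither the study participant nor the principal investigator (PI) can be blinded", and that the investigator is trained in "38% SDF application and ART, or ART alone".
- **Table 1.** The row "Caries excavation" comes directly after the allocation row. Both are marked at t0.

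On analysis, section 4 defines the intention-to-treat set as "including all randomized patients irrespective of whether they have or have not received the prescribed treatment". Section 5 brings dropouts into the analysis by multiple imputation. It does not mention patients whom the investigator excludes.

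**The concern.** If patients are randomised before excavation, the rule in 2.5.2 removes some of them after their arm is known. The plan then gives two answers to whether such a patient is analysed: 2.5.2 says out of the study, section 4 says in.

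There is also a possible route to bias. The Introduction says that improper caries removal can lead to secondary caries and failed restorations, and credits the SDF-based technique with killing persistent bacteria under the seal. An operator who knows that SDF will follow could, on that rationale, excavate less far than one who knows it will not. Excavation depth affects the chance of exposure, and so who is excluded. It also affects how much carious dentine is left, and so both primary outcomes. The blinded radiograph readers in 2.8.2 cannot correct for this, because it would arise at treatment.

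The rule removes the patient, not the tooth. Since 2.4 admits people with more than one lesion, one exposed tooth would take all of that person's teeth out.

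**Working it through.** **1. Order of events.** No sentence says when the envelope is opened relative to excavation. In favour of allocation first: the exclusion is worded as occurring during the intervention (2.5.2), excavation sits inside each arm's procedure (2.7), the code is released at the end of baseline assessment (2.12), and Table 1 puts the excavation row after the allocation row. Against: the two rows share one column (t0), and excavation is listed under the Enrolment heading rather than under Interventions. Allocation is under that same heading, however, so the heading does not establish the reverse order. Figure 1 is not available. The consistent reading is allocation first, as an inference.

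**2. Conflict with intention to treat.** On that reading, a patient with an exposure has been randomised. Section 4 includes every randomised patient whatever treatment was received; 2.5.2 excludes this one. Section 5 would resolve it only if the exclusion counted as a dropout, which it does not say.

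**3. The plan's sample size (2.11).** Inputs: effect size 0.4, alpha 0.05, power 80%, 100 per group, 10% attrition, 110 per group. The type of effect size, the test and the sidedness are not stated. I assume a standardised mean difference d = 0.4 and a two-sided test.

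- Normal approximation: n = 2 × (1.960 + 0.842)² / 0.4² = 98.1, rounded up to 99 per group.
- Exact two-sample t-test: 99.08, rounded up to 100. The stated figure is reproduced.
- After 10% attrition, 110 × 0.9 = 99 per arm. Power = Φ(0.4 × √(99/2) − 1.960) = 80.4%. This, not 100, is the baseline for comparison.

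**4. Loss of patients.** The documents give no exposure rate e, so 2%, 5% and 10% are assumptions. Evaluable n per arm = 110 × (1 − e) × 0.9, with power from the same formula.

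| e | Excluded per arm (110 × e) | Evaluable per arm | Power |
|---|---|---|---|
| 0 | 0 | 99.0 | 80.4% |
| 2% | 2.2 | 97.0 | 79.6% |
| 5% | 5.5 | 94.1 | 78.3% |
| 10% | 11.0 | 89.1 | 76.1% |

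The loss is about 1, 2 and 4 percentage points.

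**5. What unequal exclusion could do (illustration only, all inputs assumed).** Let true success be 80% in both arms, a the proportion excluded in an arm, and f the success rate the excluded patients would have had. Observed success = (0.80 − a × f) / (1 − a).

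- a = 2% versus 8%, f = 0: 0.80/0.98 = 81.6% versus 0.80/0.92 = 87.0%, a false difference of 5.3 points before rounding.
- a = 2% versus 8%, f = 0.4: 0.792/0.98 = 80.8% versus 0.768/0.92 = 83.5%, a false difference of 2.7 points.
- a = 5% in both arms with equal f: no false difference.

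**The case against.** The strongest case on the other side is that this is a wording conflict plus an unclear allocation moment, and that one sentence keeping these patients in the intention-to-treat set would settle it.

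Much of that stands. The order of allocation and excavation is inferred, as is the principal investigator being the operator, which rests on the training text in 2.12. The documents do not say that patients with an exposure leave the intention-to-treat set; they leave the question open. A reader might infer that exclusions will differ by arm. The documents do not support that: excavation is described identically in both arms and precedes SDF, so SDF cannot itself cause an exposure, and a difference would need knowledge of the arm or chance. There are also safeguards. The investigator is standardised in both treatments (2.12), teeth with pulpal involvement or large coronal loss are excluded (2.5.2), and a radiograph before the study confirms that the pulp is not involved (2.6). These should make exposures less frequent.

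Two things survive. Sections 2.5.2, 4 and 5 need reconciling even on the mildest reading, and if the reverse order was intended, 2.7, 2.12 and Table 1 need correcting instead. A sentence on the analysis set alone would also not conceal the arm from the operator during excavation, whereas moving the envelope would.

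**Conclusion.** The point holds in a limited form. As written, the plan indicates that a patient can be randomised, have a pulp exposure during excavation and be excluded, in conflict with its own intention-to-treat definition. It also allows an unblinded operator to excavate knowing the arm.

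Three stronger readings should not be drawn. The protocol does not state outright that allocation comes first. Nothing shows that exclusions or excavation depth would differ by arm; the false differences of 2.7 to 5.3 points depend entirely on the assumed 2% versus 8% imbalance and vanish when exclusion is equal. And the trial is not seriously underpowered by this rule: from 99 per arm and 80.4% power, the fall is to about 97, 94 and 89 per arm and 79.6%, 78.3% and 76.1%, given the assumed exposure rates and two-mean test. These power figures also do not carry over directly to restoration survival, which section 4 analyses by Kaplan–Meier and log-rank methods.

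The reason to act is that comparability lost in this way could not be recovered in analysis, while preventing it is nearly free.

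**What to change.** - **Timing.** In 2.12, state that the envelope is opened only after excavation of all of the patient's study teeth is complete and pulp exposure has been ruled out, immediately before the first step that differs between arms (SDF in arm 1, conditioning in arm 2). An exposure is then a screen failure before randomisation.
- **Alignment.** Reorder Table 1 so that excavation precedes allocation, describe excavation in 2.7 as a common step before the arm-specific procedures, and reword the last criterion in 2.5.2 to match.
- **Analysis set.** State in sections 4 and 5 that any patient already randomised, including one with a pulp exposure, stays in the intention-to-treat set and is handled under the missing-data plan in section 5.

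This concerns the timing of allocation and the analysis set only, not the clinical management of an exposed pulp.

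The cost is wording and an envelope opened later in the same visit, with no extra visits or staff. A few more patients may have to be screened to randomise 220: 220 / (1 − e) gives 225, 232 and 245 at the assumed 2%, 5% and 10%, that is 5, 12 and 25 more.

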### 2.7. Interventions

After patient selection, the treatment will be given to the patient according to the selection process. The study participants will be allocated to either one of two parallel arms.

Study arm 1: will receive SDF application and ART restoration.

Study arm 2: will receive ART restoration.

All treatment will be done in a dental chair.

At the baseline visit, an assessment of cavitated caries lesions will be done on all the study participants. The ADA Caries Risk Assessment Form (Age > 6) would be used to assess the risk. Depending on the study arm, ART with or without SDF will be applied to selected teeth (Figure 1). The demographic features of participants and their caries status will be recorded.

*Procedure to be followed for study arm 1:*

A preoperative photograph of the selected tooth will be taken. The caries lesion entrance will be widened and with help of a dental hatchet, the thin unsupported frangible enamel will be removed. In the next step, the decayed tissue will be excavated with a spoon excavator, first at the dentin enamel junction and thereafter from cavity walls and the pulpal floor. The cavity will then be rinsed with water and air-dried, followed by isolation with cotton rolls.

*Application of Silver Diamine Fluoride*

Using a disposable micro applicator tip, the SDF (e-SDF, 38% silver diamine fluoride, Kids-e-dental LLP, Globus Medisys, Mumbai, India) will be applied to the walls of the prepared cavity for 10 s and allowed to air dry for one minute. One drop of 38% SDF solution (2.24 F-ion mg/dose) would be required per tooth. A saturated solution of potassium iodide (Lugol’s Iodine solution 5%, Bio balance, Pali Marwar, Rajasthan, India) will be applied with a different microsponge to decrease color change and will be repeated 1-3 times until no further black discoloration is observed [17].

*Placement of ART restoration*

Glass ionomer cement (Glass Ionomer High Strength Posterior restorative, GC Corporation, Tokyo, Japan) will be prepared according to the manufacturer’s instructions. The restorative material will be placed into the prepared cavity using a plastic filling instrument. The press finger technique will be used for approximately one minute and the restoration will be coated with petroleum jelly. A carver would be used to remove the excess material. The height of restoration will be adjusted after the bite is checked using articulation paper. A photograph and a digital radiograph of the restored tooth will be taken after the procedure and at the end of the study.

*Procedure to be followed for study arm 2:*

*Placement of ART restoration*

A preoperative photograph of the selected tooth will be taken. The preparation of the cavity will be done as stated above using hand instruments. Conditioning of the prepared tooth surface will be done with an applicator tip saturated with the polyacrylic acid liquid for 10–15 s. Glass ionomer cement (GIC Fuji IX, G C CORPORATION, [name]) will be prepared according to the manufacturer’s instructions and placed into the cavity using a plastic filling instrument. The press finger technique will be followed, and the surface of the restoration will be coated with petroleum jelly. The bite will be checked using articulation paper and the occlusal adjustments will be done. A photograph and a digital radiograph of the restored tooth will be taken after the procedure and at the end of the study.

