Atraumatic restorative treatment (ART) is a highly successful community-based approach for the treatment or secondary level of prevention of dental caries. It is an alternative approach for managing dental caries which involves the removal of infected tooth tissue using conventional hand instruments alone, without the use of anesthesia and rotary equipment. One of the indications for the pertinent use of ART concerned the elderly, particularly those who are impaired. The first such study on atraumatic restorative treatment was carried out amongst elderly subjects who were housebound due to psychiatric, physical, or psychological problems. After 1 year of placement, 79% of the ART restorations were considered successful [10]. In a two-year randomized controlled trial, ART presented the probability of survival rates of 84% compared to conventional techniques, consisting of the preparation of (the decayed) tooth using a rotary instrument (for removal of infected tissues) under local anesthesia, followed by resin-modified glass ionomer cement restoration [11]. When the effect of ART on adult patients’ comfort was assessed, it was noted that ART caused less anxiety than the traditional restorative methods using rotary instruments as the vibration and sound of the rotary instruments were absent [12].

ART is an important component of the Basic Package of Oral Care (BPOC) which also includes Affordable Fluoride Toothpaste (AFT), and Oral Urgent Treatment (OUT). This has been recommended by the WHO, and has been a successful community-based approach to reducing the burden of dental caries [13]_._ Considering the global rise of the elderly population with natural dentition in the coming decennium, a study covering the effectiveness of the ART approach, as part of a package of oral care for use among the adult population, should receive serious attention. However, the ART approach is not successful in some cases, especially in cavities that are less accessible through conventional hand instruments. Improper removal of caries lesions may lead to bacterial invasion, secondary caries, and failure of restoration [14].

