### 2.8. Primary Outcomes

#### 2.8.1. Assessment of Survival of the Restoration 

The follow-up will be conducted on the 7th and 30th days, and the end of the 6th month to evaluate the survival of the restoration (Table 1).

Each restoration will be assessed according to codes and criteria used in ART studies as proposed by Jo E Frencken [13]. Cavities treated with SDF and ART will be considered arrested caries lesions when the tooth surfaces with active caries at baseline visit change into surfaces with arrested caries beneath an intact restoration. The restored tooth is asymptomatic and clinically functional.

In the SDF and ART or ART-treated tooth, if caries progress beyond the dentine, it will be considered not arrested. In such conditions, the patients will be advised to follow standard treatment protocols. During the follow-up period, if the restored tooth is extracted due to infection, trauma, or fracture, the concerned tooth will not be included in the study.

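### The arm can be known before the cavity is excavated, so excavation depth could differ by arm and bias both primary outcomes; opening the envelope after cavity preparation would close this route cheaply

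*Protocol article*

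**What the plan says.** Section 2.7 places excavation inside the arm 1 procedure: "the decayed tissue will be excavated with a spoon excavator, first at the dentin enamel junction and thereafter from cavity walls and the pulpal floor". Arm 2 takes the step over by cross-reference: "The preparation of the cavity will be done as stated above using hand instruments". Neither description gives an end point for excavation. SDF (arm 1) or conditioning (arm 2) comes afterwards.

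Section 2.12 keeps the code from the principal investigator "until the participant has been recruited into the clinical trial after all the baseline assessments are complete". In Table 1, the row "Caries excavation" stands directly below the allocation row, and both are marked at t0. Section 2.12 also states that "neither the study participant nor the principal investigator (PI) can be blinded", and that this investigator is trained and standardized in "38% SDF application and ART, or ART alone".

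On prognosis, the Introduction says: "Improper removal of caries lesions may lead to bacterial invasion, secondary caries, and failure of restoration".

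On outcomes, section 2.8.1 calls a lesion arrested when "tooth surfaces with active caries at baseline visit change into surfaces with arrested caries beneath an intact restoration". Section 2.8.2 has two independent blinded examiners compare the 6-month radiograph with the baseline one, and every radiograph is classified. The Abstract defines that baseline image as the one taken immediately after restoration, so it comes after excavation.

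**The concern.** Excavation is common to both arms and finishes before the treatments diverge, so the arm does not need to be known while it is done. The plan nevertheless allows it to be known. An operator who expects SDF to deal with remaining decay might excavate less in that arm, or might take extra care in either arm. The protocol itself treats the quality of caries removal as prognostic for later caries and restoration failure. A difference in depth would therefore carry through to both primary outcomes and be read as an effect of SDF, in either direction.

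This is performance bias. Blinded examiners would correctly record a real difference in progression, but its cause would be excavation rather than SDF. Once the cavity is filled, the clinical state of the remaining dentine can no longer be examined, and no later analysis can undo knowledge of the arm during excavation.

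**Working it through.** **Sequence, from the text**

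1. Baseline assessments are completed, and the code may then be revealed (2.12).
2. Allocation and excavation both fall at t0, with allocation listed first (Table 1).
3. Excavation follows the same wording in both arms (2.7).
4. SDF or conditioning follows, then the restoration (2.7).
5. The reference radiograph is taken after restoration (Abstract, 2.7).

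Nothing holds the code back between steps 1 and 3.

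**The plan's own sample size (2.11)**

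n per group = 2(1.960 + 0.842)² / 0.4² = 98.1, so 99. The two-sided t-test version gives 99.08, rounded up to the stated 100. With 10% attrition, 99/0.9 = 110, as stated, and 110 × 0.9 = 99 analysed per arm. The figure reproduces, and the point does not depend on it.

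**Illustration of size**

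The protocol gives no rates, so these are assumptions:

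- no SDF effect, one tooth per participant, 99 per arm, two-sided 0.05;
- progression in 5% of teeth with no soft dentine left;
- progression in p = 25% or 50% of teeth with soft dentine left;
- r = share of teeth in an arm with soft dentine left.

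Arm risk = r·p + (1 − r)·0.05. The rejection rate comes from a two-proportion z-test with pooled standard error under the null and unpooled under the alternative, counting both tails.

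Worked case, r = 20% v 40%, p = 25%:

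- Risks: 0.20 × 0.25 + 0.80 × 0.05 = 0.09, and 0.40 × 0.25 + 0.60 × 0.05 = 0.13. The spurious difference is 0.04.
- Null SE = √(2 × 0.11 × 0.89 / 99) = 0.0445. Alternative SE = √((0.09 × 0.91 + 0.13 × 0.87) / 99) = 0.0444.
- Rejection = Φ((0.04 − 1.96 × 0.0445)/0.0444) + lower tail = 0.144 + 0.002 = 14.6%.

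| r by arm | p | Risks | Spurious difference | False-positive rate |
|---|---|---|---|---|
| 25% v 30% | 25% | 10.0% v 11.0% | 1.0 points | 5.6% |
| 25% v 30% | 50% | 16.25% v 18.5% | 2.25 points | 7.0% |
| 25% v 35% | 25% | 10.0% v 12.0% | 2.0 points | 7.3% |
| 25% v 35% | 50% | 16.25% v 20.75% | 4.5 points | 13% |
| 20% v 40% | 25% | 9.0% v 13.0% | 4.0 points | 14.6% |
| 20% v 40% | 50% | 14.0% v 23.0% | 9.0 points | 37.0% |

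A second set of assumptions gives similar values. Here fully excavated teeth always count as arrested, arrest is 50–80% in the rest, and there are 100 per arm. Full excavation in 30% v 40% of teeth gives 7–12% false positives; 30% v 50% gives 14–34%.

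**The case against.** **The state after excavation is captured.** A reader might infer that what is left is never recorded, so that a difference could be neither detected nor adjusted for. The documents do not support that. The post-restoration radiograph is classified and serves as the reference for the blinded 6-month comparison, so residual radiolucency is graded for each tooth. This objection stands against the stronger reading. It does not remove the bias, because leaving more soft dentine in one arm changes the later chance of progression and the radiograph shows soft dentine only indirectly. Clinical arrest in 2.8.1 is judged against the lesion before excavation, and restoration survival has no such reference.

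**Two links are inferred.** The article does not say outright that the principal investigator operates, or that the envelope is opened before excavation. Table 1 also puts excavation above the interventions heading, as a step common to both arms. Both readings are natural, but neither is stated. What is certain is that the plan does not prevent them.

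**The instruction is already the same in both arms, and the operator is standardized.** This is true. No text asks for different excavation, and a difference in depth is a possibility, not a finding. Standardization reduces the risk but does not replace concealment at a step where concealment is feasible.

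**Dilution.** A reader might also infer that teeth with nothing left to arrest invalidate the outcome. They do dilute the contrast. If SDF acts only on residual decay (arrest 60% v 78%) and 30% of teeth in both arms are fully excavated, assumed power falls from 80% to about 60%. But the protocol describes a comparison in a pragmatic setting, and well-excavated teeth belong to that question. A clean tooth can also develop new radiolucency, so it is not arrested by definition. This is a matter of interpretation, not an error in the design.

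**Record forms are not shown.** A per-tooth field might exist on them, so its absence from a condensed article is not held against the plan. The timing of code release is different, because the article does state it.

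**Conclusion.** The point holds as a gap in concealment at one step. Excavation is identical in both arms and is prognostic on the protocol's own account, yet it may be done with the arm known by an operator who is not blinded. Blinded radiographic reading and the graded post-restoration image limit the problem without closing it.

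The size cannot be derived from the documents. Under the stated assumptions the false-positive rate is close to nominal (5.6–7.0%) for a 5-point arm difference in residual soft dentine, 7–13% for 10 points and 15–37% for 20 points. Nothing in the protocol shows that any such difference will occur. The conclusion also rests on the inferences that the principal investigator operates and that the code is opened before excavation. The change is worth making because it is cheap and cannot be replaced by a later analysis. It is a cheap improvement and not evidence that the planned comparison is invalid.

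**What to change.** In sections 2.7 and 2.12 and Table 1:

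1. State that the sealed envelope is opened only after all of the participant's study teeth have been excavated and prepared, and before SDF or conditioning. All teeth must be included because participants are randomized and may have several lesions. If some teeth were excavated after opening, the record in step 2 would be taken with the arm known and would no longer be a baseline covariate.
2. At that moment, record for each tooth whether dentine penetrable by the CPI probe remains (yes/no), using the probe test already in section 2.6.
3. In section 4, name this record as a prespecified baseline covariate in the arm comparisons of caries arrest and restoration survival, and report arrest by this stratum as well.

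No rule on how far to excavate is needed or proposed; that stays a clinical decision, made without knowledge of the arm.

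The cost is an envelope opened mid-procedure, which needs someone at the chair to hand it over, slightly more chair time (more for participants with several study teeth), one extra field per tooth and one more reported stratum. No extra participants or radiographs are required.
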